##### Intercurrent event strategy

Intercurrent events describe circumstances occurring after randomisation that preclude outcome observation or affect its interpretation. We have pre-specified possible intercurrent events and devised strategies for their handling:

Inadequate study drug adherence: Given that establishing biological efficacy is the primary objective of the trial, all participants who achieve at least 80% study medication compliance and provide a 180-day blood sample will be included in the primary efficacy analysis (principal stratum strategy). As a supplementary estimand, we will also perform a dose-response analysis in all participants who provide a blood sample within the required time period (regardless of medication compliance)COVID-19 infection: The main analysis of the primary estimand will include participants with COVID-19 infection. As a first sensitivity analysis for the primary estimand, we will perform the primary analysis excluding participants with confirmed COVID-19 infection before or during the study.Inability to collect sample for primary outcome: As a supplementary analysis for the primary estimand, the missingness at random assumption will be evaluated for any patient or system related intercurrent events preventing the collection of the primary outcome. A sensitivity analysis using a pattern mixture model will be undertaken.

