### Study Estimands

#### Primary estimand

Population: all included participants.Individual level outcome measure: percentage change in plasma p-tau181 concentration (comparing baseline to 180 days). P-tau181 levels will be measured using the single-molecule array (Simoa) technique according to the manufacturer’s instructions (Quanterix Corp., US).Population level outcome measure: difference in means between intervention and control groups adjusted for baseline p-tau181 level.

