### Sample size

Allowing for potential participant attrition, the total sample size for the study is 60 (30 per arm). Sample size calculations assumed a two-tailed alpha of 0.05 and a similar baseline standard deviation between the two arms. A total sample size of 52 participants (26 per arm) would yield 80% power to observe a large treatment effect (Cohen’s d 0.8). This sample size estimation is conservative in the sense that including the baseline p-tau181 concentration in the final ANCOVA model would increase the power.

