### Statistical analysis

All outcomes and analyses are prospectively categorized as primary, secondary or exploratory. Differences in all endpoints between the 2 arms of the study will be tested independently at the two-tailed 0.05 level of significance. All estimates of treatment effects will be presented with 95% confidence intervals. The primary endpoint will be tested using an ANCOVA model with treatment arm as an independent variable and baseline blood p-tau181 concentration as a covariate. Between group differences in secondary and exploratory outcomes will be assessed using regression models as appropriate to the response outcome distribution using baseline values of the respective outcomes as adjustment covariates. The detailed analysis will be prespecified in a formal statistical analysis plan which will be finalised prior to the study database lock.

No formal adjustments will be undertaken to constrain the overall type I error associated with the secondary and exploratory analyses. Their purpose is to supplement evidence from the primary analysis to characterize the treatment effect more fully. Results from the secondary analyses will be interpreted in this context.

Given that establishing biological efficacy is the primary objective of the trial, according to the pre-specified estimand, all participants who achieve at least 80% study medication compliance and provide a 180-day blood sample will be included in the primary efficacy analysis. All participants who provide both baseline and end of treatment blood samples will be included in a secondary dose-response analysis to account for potential early study withdrawals or poor compliance.

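### The primary p-tau181 analysis is a per-protocol comparison labelled a principal stratum, and no efficacy comparison by randomised arm regardless of adherence is described

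*Protocol article*

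**What the plan says.** The Primary estimand section opens with "Population: all included participants". Its Intercurrent event strategy then limits the primary efficacy analysis to those with "at least 80% study medication compliance and provide a 180-day blood sample will be included in the primary efficacy analysis (principal stratum strategy"). The reason given is "Given that establishing biological efficacy is the primary objective of the trial". The Statistical analysis section repeats the rule: "all participants who achieve at least 80% study medication compliance and provide a 180-day blood sample will be included in the primary efficacy analysis". The only model stated is an "ANCOVA model with treatment arm as an independent variable and baseline blood p-tau181 concentration as a covariate".

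Three other analyses of the primary outcome are described:

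- a dose-response analysis in everyone who provides a sample, whatever their compliance (called supplementary in the estimand section and secondary in Statistical analysis);
- a sensitivity analysis that removes participants with confirmed COVID-19;
- an evaluation of the missing-at-random assumption with a pattern mixture model, for samples that could not be collected.

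The legend of Figure 3 places endpoint collection in the last 10 days of the participant's 180 days on study drug. On numbers, the Sample size section says "Allowing for potential participant attrition, the total sample size for the study is 60 (30 per arm"), with 52 (26 per arm) giving 80% power at Cohen's d 0.8.

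**The concern.** A principal stratum here would be the people who would adhere whichever arm they were assigned to. The plan instead keeps those seen to adhere to SAMe in one arm and those seen to adhere to placebo in the other. These are the same kind of patient only if whatever lowers pill-taking (tolerability, illness, cognitive decline) works alike in both arms. Randomisation does not secure that, and the stated ANCOVA adjusts only for baseline p-tau181.

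The dose-response analysis does not fill the gap, because the amount of drug taken is itself determined after randomisation. The pattern mixture model addresses absent samples, not participants who gave a sample but took less than 80% of their drug. A reader of the results could therefore not tell whether the primary finding survives in the arms as randomised. The article's conclusion looks to this result to support a phase III trial.

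**Working it through.** **1. The population statements compared.** Estimand population: all included participants. Analysis set: "all participants who achieve at least 80% study medication compliance and provide a 180-day blood sample". These differ by every participant below 80% compliance and every participant without a sample.

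**2. The plan's own figure.** Two-sample t-test, two-sided alpha 0.05, noncentral t with nc = d × √(n₁n₂/(n₁+n₂)). For 26 per arm and d = 0.8: nc = 0.8 × √13 = 2.884, df = 50, power 80.7%. At 25 per arm it is 79.1%. The stated 52 reproduces. The allowance is (60 − 52)/60 = 13.3%.

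**3. Possible bias with no drug effect.** The protocol gives no adherence rates, so these inputs are assumptions. If a share q of an arm is excluded and is worse than the kept participants by g SD, the kept mean is shifted by q × g. Placebo is assumed to lose 10% at random (27 kept).

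| SAMe excluded | gap g | bias (SD) | kept, SAMe/placebo | nc | type I error |
|---|---|---|---|---|---|
| 20% | 0.5 | 0.20 × 0.5 = 0.10 | 24 / 27 | 0.356 | 6.4% |
| 25% | 0.8 | 0.25 × 0.8 = 0.20 | 22.5 / 27 | 0.701 | 10.6% |
| 25% | 1.0 | 0.25 × 1.0 = 0.25 | 22.5 / 27 | 0.876 | 13.8% |

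Biases of 0.20 and 0.25 SD are 25% and 31% of the planned d of 0.8.

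**4. Cross-check by simulation.** 30 per arm, no treatment effect, 40,000 runs, exclusion driven by a latent factor correlated ρ with the outcome.

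- Same mechanism and rate in both arms (10% or 20%): rejection about 5%.
- 20% against 5% excluded: 6.0%, 7.3% and 9.3% for ρ = 0.3, 0.5 and 0.7.
- 30% against 5% excluded: 7.0%, 10.6% and 16.6%.

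The nominal level thus depends on selection acting alike in the two arms.

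**5. Power under each choice.** Assumptions: d = 0.8 in adherers, no effect in non-adherers, all 60 sampled for the by-arm analysis, and the same non-adherence q in each arm. By-arm effect = 0.8 × (1 − q); restricted n = 30 × (1 − q) per arm.

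| q | by-arm d | by-arm power (30 per arm) | restricted n per arm | restricted power |
|---|---|---|---|---|
| 10% | 0.72 | 78.3% | 27 | 82.2% |
| 20% | 0.64 | 68.4% | 24 | 77.4% |
| 30% | 0.56 | 56.9% | 21 | 71.6% |

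The restricted set falls below 26 per arm once low adherence and missing samples together exceed 13.3%.

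**The case against.** The restriction is deliberate and openly stated: in a 60-person phase II biomarker study, asking what the drug does when taken is a legitimate question. Double blinding and a study partner who oversees dosing limit differential non-adherence, and the human AD experience cited reports excellent tolerability, though for combination products. The detailed analysis is deferred to a statistical analysis plan that is not shown. A by-arm primary would cost power, and considerably so if non-adherence were high.

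Most of this stands as mitigation. It explains the target but does not turn observed adherers into a principal stratum. Nor can the matter be left wholly to the later plan, because the protocol already fixes the set, the label and the model.

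Two stronger readings go too far. One is that nothing in the trial compares the arms without the 80% filter. The safety estimand does: it compares the proportions with serious adverse events in everyone who took at least one dose. The gap concerns efficacy. The other is that the trial is underpowered because the allowance ignores non-adherers. The Sample size section does not break down attrition, so that cannot be established, and it also expects a gain from baseline adjustment that the t-test figures leave out.

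**Conclusion.** The point holds as a mislabelled analysis set, an unreconciled estimand population and a missing by-arm p-tau181 comparison. It should be fixed.

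A reader might go further and infer that the primary result will be biased, or that a positive result would be an artefact. The documents do not support that. They give no adherence rate, no difference between arms and no link between pill-taking and p-tau181. The 6% to 14% range describes what could happen under the assumed differential exclusions; the error stays at 5% if selection is alike in both arms, and neither size nor direction can be derived from the protocol.

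Nor does it follow that the declared biological-efficacy target must be abandoned. Whether the by-arm comparison becomes primary or stands beside the present analysis is partly a trade between protection from selection and power.

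**What to change.** 1. Prespecify the same ANCOVA by assigned arm in all randomised participants regardless of adherence. Preferably make it primary; at minimum report it beside the current analysis as the test of whether the result survives.
2. Handle missing samples under a stated assumption, building on the pattern mixture model already planned. Restricting to those with a sample would still condition on a post-randomisation event.
3. State that the endpoint sample is also sought at about 180 days from randomisation in people who have stopped study drug; the Figure 3 legend ties it to time on drug.
4. Rename the 80% set per-protocol, or use a genuine complier or principal-stratum estimator with its assumptions written out. Using randomised arm as an instrument requires assignment to have no effect in those classed as non-adherent, which is doubtful for someone who took, say, 70% of the drug.
5. Make the population in the Primary estimand section agree with the Intercurrent event strategy and Statistical analysis sections.
6. State that the 8/60 = 13.3% allowance must cover every loss from the 80% set, low adherence included.

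Cost: mostly wording, which can be settled before the analysis plan is finalised ahead of database lock, plus a small visit-schedule change to sample people off drug. No extra participants are needed if the by-arm analysis is reported alongside. If it becomes primary, the price is the power loss in the second table: about 4 percentage points at 10% non-adherence (82.2 − 78.3), 9 at 20% (77.4 − 68.4) and 15 at 30% (71.6 − 56.9).

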**Figure 3 Fig3:**
[figure not shown]
Summary of SAMe Study design. Participants will complete 6 study visits

Each blue column summarizes the visit number, its timing and key purpose, and the study activities performed during the interaction. Visit 1 comprises obtaining informed consent, screening for eligibility, enrollment if suitable, and baseline data collection. Randomization and study drug dispensation occurs at visit 2, which constitutes ‘day 0’. Visits 3 and 4 involve safety assessments. Endpoint data collection occurs at visit 5. Visit 6 entails a follow-up telephone call to the participant for a final adverse event report. Visits will occur within an allowed range of days around the desired timepoint (indicated by ±). The endpoint data collection visit (visit 5) does not have an upper allowable bound: endpoint data is to be collected within the final 10 days of the participant’s 180 days taking the study drug. *:vital signs, body weight, physical examination; @: full blood examination, general biochemistry, liver function tests, coagulation studies, vitamin B12, folate, homocysteine; ^: Repeatable Battery for the Assessment of Neuropsychological Status, Standardized Mini-Mental State Examination, Cognitive Dementia Rating, California Verbal Learning Test 3rd Edition, Montreal Cognitive Assessment, Digit Symbol Substitution Test, Geriatric Depression Scale. ApoE: apolipoprotein E; CDR: Cognitive Dementia Rating; p-tau181: phosphorylated tau181; SAMe: S-adenosyl methionine.

The trial has been prospectively registered on australianclinicaltrials.gov.au (ACTRN12620000506998) and will be conducted within the estimand framework for the design and analysis of clinical trials. Briefly, the objective of the estimand framework is to align the clinical trial objectives with the study design, endpoints and analysis, in order to improve study planning and the interpretation of study results (26). The trial design and estimands include prespecified strategies for the conduct of the trial during the COVID-19 pandemic (27–29). The protocol is reported according to SPIRIT guidelines, modified through inclusion of estimand framework (30).

This study will be conducted in accordance with the Declaration of Helsinki and Council for International Organizations of Medical Sciences International Ethical Guidelines. The protocol has been approved by the local Human Research Ethics Committee.

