### Intervention

Participants will be instructed to take the assigned treatment once a day for a period of 180 days as an adjunct to their Alzheimer’s disease standard of care. No dose reductions will be considered.

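### No p-tau181 comparison of the randomised arms regardless of compliance is stated; the only stated analysis that keeps low compliers is a dose-response, which randomisation may not protect

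*Protocol article*

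**What the plan says.** Under the primary estimand's intercurrent event strategy, "all participants who achieve at least 80% study medication compliance and provide a 180-day blood sample will be included in the primary efficacy analysis"; the article labels this a principal stratum strategy. The Statistical analysis section repeats the restriction.

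The participants left out are addressed by one other analysis, described twice:

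- Intercurrent event strategy (as a supplementary estimand): "we will also perform a dose-response analysis in all participants who provide a blood sample within the required time period", whatever their compliance.
- Statistical analysis (as a secondary analysis): "All participants who provide both baseline and end of treatment blood samples will be included in a secondary dose-response analysis", with the aim "to account for potential early study withdrawals or poor compliance".

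The Randomization section gives one active regimen, 400 mg once daily, against placebo. The Intervention section adds: "No dose reductions will be considered". On timing, the Figure 3 legend states that "endpoint data is to be collected within the final 10 days of the participant’s 180 days taking the study drug".

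Neither description defines the dose variable, the model or the role of assigned arm.

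**The concern.** The primary analysis set is chosen by behaviour after randomisation. A reader will therefore look for a companion analysis that compares the arms as randomised, including those who took too little drug. For p-tau181 none is stated. The COVID-19 sensitivity analysis repeats the primary analysis in a smaller set, and the pattern mixture analysis concerns samples that could not be collected.

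What is stated is a dose-response. Only one dose is assigned, so within the active arm dose can only mean drug taken. If those who take less also differ in prognosis, a slope on drug taken mixes that difference with any drug effect. The analysis offered as the answer to poor compliance could then show a gradient when the drug does nothing.

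**Working it through.** **1. The plan's own figure.** Inputs from the Sample size section: d = 0.8, two-sided alpha 0.05, 26 per arm, 80% power; 60 enrolled. For a two-sample t-test, power comes from the noncentral t with 2n - 2 degrees of freedom and noncentrality d x sqrt(n/2). With n = 26 the noncentrality is 0.8 x sqrt(13) = 2.88 and power is 80.7%. With n = 25 it is 79.1%. So 26 per arm reproduces, and the allowance for attrition is 8/60 = 13.3%. The point does not rest on a wrong figure.

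**2. Which p-tau181 analyses keep participants below 80% compliance?**

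| Analysis | Keeps them? | Compares arms? |
|---|---|---|
| Primary ANCOVA | No | Yes |
| COVID-19 sensitivity analysis | No (repeats the primary) | Yes |
| Pattern mixture sensitivity analysis | Population not stated | Not stated |
| Dose-response | Yes | Not stated |

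**3. How far could a dose-response mislead?** The documents give neither an adherence rate nor a link between adherence and outcome, so everything here is assumed. Simulated trials have 30 per arm and no drug effect. Each participant has a prognostic factor u.

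- Outcome = -rho x u + noise.
- Adherence = 0.85 + 0.15v, clipped to 0-1, where v has correlation L (the link) with u.
- About 37% of participants then fall below 80% compliance.

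Percentage of trials with p < 0.05 for the slope on drug taken within the SAMe arm:

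| Link L | rho 0.3 | rho 0.4 | rho 0.5 |
|---|---|---|---|
| 0.3 (weak) | 8 | 9-10 | 12 |
| 0.5 (moderate) | 12 | 18 | 25 |
| 1 (adherence is the factor) | 34-36 | 59-60 | 79-80 |

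Where two values are shown, separate runs differed by simulation error. With both arms in the model and placebo coded as dose zero, rejection is about 6%, 7% and 8% at L = 1 and close to 5% at the weaker links. The by-arm test stays near 5% throughout.

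**4. A second form of model.** This check used a different compliance distribution (Beta(6,1), fully tied to the factor), baseline adjustment and 4,000 trials. Rejection at correlations 0.2, 0.4 and 0.6:

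| Model | 0.2 | 0.4 | 0.6 |
|---|---|---|---|
| Slope within the active arm | 16.4% | 54.7% | 91.9% |
| Dose term added to arm | 16.6% | 54.7% | 90.0% |
| Placebo coded as zero | 5.0% | 6.2% | 8.6% |
| By randomised arm | 4.6% | 5.2% | 5.3% |

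Adding arm to the model does not rescue the dose term.

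**5. What the by-arm analysis costs in power.** Assume all 30 per arm are sampled and a fraction q of the active arm gets no effect, so the effective d is 0.8 x (1 - q).

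- q = 0: d = 0.80, power 86.1%.
- q = 13.3%: d = 0.69, power 75.2%.
- q = 20%: d = 0.64, power 68.4%.
- q = 30%: d = 0.56, power 56.9%.

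If non-adherers instead get half the effect, q = 20% gives 78.3%.

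**The case against.** The strongest reply is that the model is not given. The article defers detail to a statistical analysis plan, and an instrumental-variable estimate could itself be called a dose-response. That stands. A reader might infer that the planned analysis is certainly a confounded slope, but the text does not say so, and a model across both arms with placebo at zero is close to nominal. What survives is that nothing in the text rules out the vulnerable forms, and that the stated companion analysis is not the arm comparison.

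The link between adherence and prognosis is also an assumption. The inclusion criteria require a study partner to oversee drug administration, and the outcome is a percentage change adjusted for baseline; both weaken it. The 34-80% range is therefore a worst case, not an expectation.

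Two further readings are tempting and go too far:

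- That this is the only analysis in the trial that keeps non-adherers. The safety estimand keeps anyone with at least one dose, so the statement holds for p-tau181 efficacy only.
- That the two descriptions define clearly conflicting populations. The Statistical analysis section does not say that any end-of-treatment sample will do, and the Figure 3 legend describes a single endpoint visit. If both phrases mean that visit, the sets nearly coincide. What remains is a difference in label, and a stated aim of covering early withdrawals that fits only those who stop the drug yet still give the endpoint sample.

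Finally, the primary test is untouched. A spurious gradient could not by itself make the trial positive.

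**Conclusion.** The point holds in a limited form. For p-tau181 the article states no comparison of randomised arms regardless of compliance. The dose-response that stands in its place is not shown to preserve randomisation. Any slope within the active arm, or any dose term beside arm, would lack that protection, because drug taken is decided after randomisation.

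The false-positive rate of such a slope could be little above nominal or very high. The answer turns on the unstated model and on an adherence-prognosis link about which the documents are silent. This is a change the sponsor should make. It does not show that the primary analysis will give a wrong result.

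**What to change.** In both the primary estimand's intercurrent event strategy and the Statistical analysis section, state as the supplementary analysis the baseline-adjusted ANCOVA by randomised arm in all randomised participants with baseline and endpoint p-tau181 samples, regardless of compliance. If an exposure effect is wanted, estimate it by two-stage least squares with randomised arm as instrument and drug taken as exposure, not by a slope on compliance.

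Align the two sections on one population and one status (supplementary or secondary). Say whether participants who stop treatment early are still sampled at the day-180 visit. One section says the analysis accounts for early withdrawals, while the other requires a sample in the window, which the Figure 3 legend ties to the final days on study drug.

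The cost is wording; for participants already due to be sampled, no new data are needed. The by-arm estimate is diluted by non-adherence, with power of about 86% undiluted and about 68% if an assumed 20% get no effect, which is tolerable for a supplementary analysis. The instrumental-variable interval will be wider than that of a compliance slope.
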